#### Frequency and volume

Following the updated physical activity guidelines, children and adolescents should include bone-strengthening exercises as part of the daily physical activity on at least 3 days per week. Participants in the iBoneFIT study will perform the exercise programme three to 4 days per week (preferably on Mondays, Wednesdays and Fridays; or Mondays, Tuesdays, Thursdays and Fridays). If one training session is missed, the participant will be able to do it on a different day of the week, provided a minimum of 24 h of rest.

The total volume will be 7296 squat/jumps (2000 squats + 5296 jumps). The doses will be composed of 136 sessions (10–20 min/session) over 36 weeks. A full description of the training volume and its progression is shown in Table 3. In a recent 9-month RCT based on jumping activities with similar dosage we reached 70% of compliance (6216 jumps), and this was enough to improve bone outcomes in non-weight-bearing sport athletes [38]. Thus, the proposed volume of 7296 squat/jumps is likely to elicit the same effect in paediatric cancer survivors.

**Table 3 Tab3:** iBoneFIT study exercise programme periodisation

Phase	Warm up^**a**^	Exercise^**b**^	Level	Repetitions	Sets a day (Rest^**c**^)	Sessions a Week	Squats/Jumps a Week
**1**	RAMP	BM-based Squat	1 (1–4 wk)	15	3	4	180
			2 (5–8 wk)	20	4	4	320
**Total phase 1 (8 wk)**							2000
**2**	RAMP	SJ	1 (9–12 wk)	10	3	3	90
			2 (13–16 wk)	15	3	4	180
			3 (17–20 wk)	20	4	4	320
**Total phase 2 (12 wk)**							2360
**3**	RAMP	CMJ	1 (21–24 wk)	10	3	3	90
			2 (25–28 wk)	12	3	4	144
			3 (29–32 wk)	15	3	4	180
			4 (33–36 wk)	20	4	4	320
**Total phase 3 (16 wk)**							2936
**Total intervention (36 wk)**							7296

*RAMP* raise, activate, mobilise and potentiate, *BM* body mass, *SJ* squat jump, *CMJ* countermovement jump

^a^Warm up will be focused on dynamic exercises with progressive intensity enhancing optimal core body temperature, motor unit excitability, kinesthetic awareness and ranges of motion

^b^Each exercise will be suggested to be performed at the pace of the personal trainer managing the session. If not, a self-paced performance will be recommend

^c^Phase 1 rest = 45 s

Phases 2 and 3 rest = 1 min

#### Periodisation

Although Peitz et al. [59] did not find differences between no, linear and undulating periodisations in youth, iBoneFIT will implement a linear model based on the fact that variation in volume and/or impact loading within the programme phases may stimulate greater bone adaptions and reduce boredom and risk of over-training [44]. The exercise programme will be divided in three phases of different durations and impact loadings (i.e. height reached in the different jumps). Each phase will be composed of levels with progressive increase in volume (i.e. repetitions, sets per day and sessions per week) as shown in Table 3 (Item 7b).

The phase 1 corresponds to the first 8 weeks of the exercise programme. Participants will perform body mass-based squats and the volume will increase progressively by modifying the number of repetitions and sets per day. Paediatric cancer survivors may present reduced aBMD and muscular fitness [60], therefore jumping exercise prescription may not be safe. In this sense, body mass-based squat was chosen in this phase following previous studies that observed positive effects on muscular fitness after an 8-week intervention [61, 62].

The phase 2 will last 12 weeks and participants will perform squat jumps. In this phase, the volume will increase progressively by modifying the number of repetitions, sets per day and sessions per week. Squat jump has been chosen as intermediary exercise before the use of countermovement jump since the jump height reached is lower and hence, ground reaction forces produced at the landing are lower [63]. Furthermore, squat jump training reduces the degree of muscle slack on the push-off phase [64] which could supply a better execution of the countermovement jump afterwards.

The phase 3 will be the longest phase of the exercise programme with 16 weeks. Participants will perform countermovement jumps and the volume of this phase will be increased progressively by modifying the number of repetitions, sets per day and sessions per week. Countermovement jump will be chosen in this phase since it produces a huge force application (~ 400 times body mass / second) and ground reaction forces (~ 5 times body mass) in youth [65, 66]. Countermovement jump has been previously reported to be valid and reliable in children [67].

#### Session structure

The structure of the exercise sessions will be: 1) warm up; 2) squat/jumps training; 3) cool down. Briefly, the warm ups will be based on RAMP methodology (i.e. raise, activate, mobilize and potentiate) in order to maximize middle-term performance of the main exercises (i.e. squat/jumps exercises) [68]. Eight exercises focused on the brace, squat, lunge or jump patterns will be included in this part of the session. Squat/jumps training will comprise body mass-based squats, squat jumps and countermovement jumps in phase 1, phase 2 and phase 3, respectively. Finally, participants will perform a cool down including static stretching and relaxing exercises (Item 8).

### Control group

Participants randomly allocated to the CG will receive information on the recommendations of calcium and vitamin D [69]. Educational leaflets and infographics based on the current recommendations [69] will be delivered to the participants at the beginning of the study (Item 10). After finishing the study, they will be offered the same online exercise programme.

## Outcomes

The primary outcome of our study is bone health. The secondary outcomes include anthropometric measurements, body composition, physical fitness components, free-living physical activity, blood samples, calcium and vitamin D intake, health-related quality of life and mental health. Assessments will be conducted at baseline, repeated at post-test (i.e. after 2 weeks of intervention or control condition at most) and follow up (i.e. after 4 months of intervention or control condition). Participants will be assessed for the post-test and follow up following the order through which they will be tested at baseline, to avoid cofounding by time between baseline and the other assessments.

Data obtained on the assessments will be recorded on a paper print-out and entered into an Excel file for future statistical analysis. Questionnaires will be filled using Google Forms which allows us to record the data without hand-written management. In compliance with the Personal Information Protection Act, the names of all participants will not be disclosed, and an identifier number will be used to identify each participant. All participants will be informed that the clinical data obtained in the trial will be stored in a computer and will be handled with confidentiality.

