**Methods:**

A minimum of 116 participants aged 6 to 18 years will be randomized into an intervention (*n* = 58) or control group (*n* = 58). The intervention group will receive an online exercise programme and diet counselling on calcium and vitamin D. In addition, five behaviour change techniques and a gamification design will be implemented in order to increase the interest of this non-game programme. The control group will only receive diet counselling. Participants will be assessed on 3 occasions: 1) at baseline; 2) after the 9 months of the intervention; 3) 4 months following the intervention. The primary outcome will be determined by dual energy X-ray absorptiometry (DXA) and the hip structural analysis, trabecular bone score and 3D-DXA softwares. Secondary outcomes will include anthropometry, body composition, physical fitness, physical activity, calcium and vitamin D intake, blood samples, quality of life and mental health.

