### Sample size

We have used femoral neck aBMD as the outcome to calculate the sample size, since it is a key variable in the diagnosis of osteoporosis. Since the study will include children and adolescents (6–18 years), the sample size has been calculated taking into account that sub-group analysis by age groups (6 to 11 years and 12 to 18 years) may be required. Based on an expected effect size of 0.25 for the change in femoral neck aBMD, an α level of 0.05 and a power of 80%, a minimum of 116 participants will be required (IG = 58 and CG = 58). This includes a 20% extra for occasional losses and refusals and 10% for multivariable analyses. Calculations have been obtained using G*Power (v.3.1.9.2) with analysis of variance: repeated measures (within-between interactions) for 2 groups (between factors) and 2 time points (pre, post, within factors). A correlation between measures of 0.7 has been assumed, which is achievable when measuring bone outcomes [16].

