### Primary outcome: bone health

#### Dual-energy X-ray Absorptiometry (DXA)

A DXA (Hologic Series Discovery QDR, Bedford, MA, USA) will be used throughout the study to obtain BMC (g) and aBMD (g/cm^2^) for the hip, lumbar spine and total body less head. Furthermore, lean soft tissue mass (g), fat mass (kg) and body fat percentage (%) for the whole body will be obtained from total body scans. APEX software (version 4.0.2) will be used to analyse the scans following the recommendations for children and adolescents [70]. Equipment calibration, participant setting and scan analyses will be performed by the same researcher. DXA uses a minimal radiation (i.e. spending a day outside in the sunshine) and the effective dose for the scans in children has been set in 3–6 μSv [71].

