##### Hip Structural Analysis (HSA)

HSA is a DXA-based software that analyses hip scans to estimate bone geometric properties of the proximal femur. This software analyses structural characteristics through the distribution of bone mineral mass in a line of pixels across the bone axis [72]. These geometric estimates in the proximal femur will be derived from: 1) the cross-sectional area (mm^2^); 2) section modulus (mm^3^); and 3) the cross-sectional moment of inertia (mm^4^). For these variables, the short-term coefficient of variation has been reported to be between 2.4 and 10.1% [73].

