##### Trabecular Bone Score (TBS)

TBS is a DXA-based software (iNsight version 3.0, Medimaps, Pessac, France) that indirectly assesses the state of trabecular microarchitecture in the lumbar spine. Based on experimental variograms of the projected DXA image, TBS evaluates the heterogeneity of the grey-levels pixels of the aBMD and higher heterogeneity implies worse trabecular connectivity [74]. Low values reported in this parameter have been associated with a higher fracture risk, and therefore it is considered an index of bone quality [75]. The short-term coefficient of variation for TBS has been reported to be between 1.7 and 2.1% for spine aBMD in 92 individuals with repeated spine DXA scans performed within 28 days [76].

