##### 3D-DXA Modelling

3D-SHAPER is a DXA-based software (version 2.2, Galgo Medical, Barcelona, Spain) that derives 3D analyses from the hip DXA scans. Details of the model algorithm are published elsewhere [77]. Briefly, this software uses a 3D statistical shape and density of the proximal femur built from a database of quantitative computed tomography (QCT) scans of Caucasian population [77]. The 3D-SHAPER will assess bone parameters such as the cortex, the femoral shape and the trabecular macrostructure [78].

The cortex is segmented by fitting a mathematical function of the cortical thickness (mm), cortical volumetric BMD (cortical vBMD, mg/cm^3^), the location of the cortex, the density of surrounding tissues and the imaging blur to the density profile computed along the normal vector at each node of the proximal femur surface mesh [78]. In addition, the cortical surface BMD (cortical sBMD, mg/cm^2^) is computed at each vertex of the femoral surface mesh, as the multiplication of the cortical thickness (cm) by the cortical vBMD along its thickness [79]. Any increase in either cortical thickness or cortical vBMD will ensure an increase in cortical sBMD. Nevertheless, if cortical thickness and cortical vBMD vary in opposite ways, cortical sBMD will remain unchanged. All measurements will be computed over the total femur (i.e. the shaft, the intertrochanteric and the union of the neck) according to the trabecular, cortical and integral compartments.

Correlation coefficients between BMD computed by 3D-SHAPER and QCT of the total femur have been reported to be 0.86–0.95, whereas the correlation coefficients of BMD computed by 3D-SHAPER with BMD computed by QCT have been reported to be 0.91 [77]. The short-term coefficients of variations of aBMD measurements have been reported to be 1.5, 4.5, 1.7 and 1.5% for cortical thickness, trabecular vBMD, cortical vBMD and cortical sBMD, respectively [79].

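### The primary outcome is a domain of at least 14 bone measures with none declared primary, although the trial is sized on femoral neck aBMD

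*Protocol article*

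**What the plan says.** The protocol article describes the primary outcome in three places and names no deciding variable in any of them.

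- **Abstract, Methods:** "The primary outcome will be determined by dual energy X-ray absorptiometry (DXA) and the hip structural analysis, trabecular bone score and 3D-DXA softwares".
- **Outcomes:** "The primary outcome of our study is bone health".
- **Primary outcome section:** the heading again gives only bone health. The subsections then list measures. DXA is used "to obtain BMC (g) and aBMD (g/cm^2^) for the hip, lumbar spine and total body less head". Hip structural analysis gives cross-sectional area, section modulus and cross-sectional moment of inertia. The trabecular bone score "indirectly assesses the state of trabecular microarchitecture in the lumbar spine". The 3D-DXA subsection gives precision figures "for cortical thickness, trabecular vBMD, cortical vBMD and cortical sBMD, respectively", and says that measurements are computed "according to the trabecular, cortical and integral compartments".

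The Sample size section takes a single variable: "We have used femoral neck aBMD as the outcome to calculate the sample size". Its reason is that variable's role in diagnosing osteoporosis, and it sets alpha at 0.05 and power at 80%.

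The Statistical analysis section applies one general linear model approach, the group-by-time interaction from baseline to 9 months, to primary and secondary outcomes alike. Bone outcomes enter as age- and sex-adjusted z-scores, with the baseline value as covariate. No deciding variable is named and no test level is given there.

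**The concern.** A confirmatory trial needs to say in advance which comparison decides its question. Here the hypothesis, at the end of the Background, is that the programme improves bone health, and the declared primary outcome is equally broad. Femoral neck aBMD is singled out for sizing, but the outcomes sections list only the hip as a site and never mention the femoral neck.

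Two things are at stake. First, a later report could rest its main claim on whichever of the listed measures reaches significance, and a reader could not show from this plan that another one was intended. Second, the stated power belongs to one variable, so it is unclear whether it describes the test that will carry the conclusion.

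**Working it through.** **1. The plan's own figure.** The plan gives no error rate for its primary family, so there is none to reproduce. Its one figure near this point is the sample size of 116, computed for femoral neck aBMD alone. Taking 0.25 as Cohen's f, with a correlation of 0.7, two groups, two time points and alpha 0.05, the noncentrality is λ = f² × N × m / (1 − ρ). At N = 22 in total this is 0.0625 × 22 × 2 / 0.3 = 9.17, which gives power of 82%. Two age groups with 20% and 10% inflation give 22 × 2 × 1.2 × 1.1 = 58 in total. The value 116 appears only if 22 is read as a per-arm number (4 × 22 × 1.32 = 116.2). That discrepancy is a separate matter and does not bear on this point. What matters here is that the calculation uses one variable and one test.

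**2. Count of measures under the primary heading.**

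| Source | Bone measures | Running total |
|---|---|---|
| DXA: BMC and aBMD at three sites | 6 | 6 |
| Hip structural analysis | 3 | 9 |
| Trabecular bone score | 1 | 10 |
| 3D-DXA: cortical thickness, trabecular vBMD, cortical vBMD, cortical sBMD | 4 | 14 |

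Counting an integral vBMD makes 15. Lean mass, fat mass and body fat percentage also appear in the DXA subsection, but they are not bone measures and are left out. Hip sub-regions are not listed and are not counted.

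**3. Error rate if any one measure counted as success.** This success rule is an assumption. So is testing each measure at two-sided 0.05, the only level in the document, which appears only under Sample size.

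- Independent tests: 1 − 0.95^14 = 51.2% (15 measures: 1 − 0.95^15 = 53.7%).
- Independent tests, false positive favouring exercise only: 1 − 0.975^14 = 29.8%.
- Correlated tests: Z_j = √ρ·U + √(1 − ρ)·e_j for 14 measures, with U and e_j standard normal, in 400,000 simulated draws. An error is any |Z_j| > 1.96, or any Z_j > 1.96 for one favouring exercise. The document gives no correlations between outcomes, so a range is shown.

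| Assumed ρ | At least one false positive | At least one favouring exercise |
|---|---|---|
| 0.3 | 43.6% | 22.3% |
| 0.5 | 34.7% | 17.5% |
| 0.7 | 24.9% | 12.5% |
| 0.8 | 19.6% | 9.8% |
| 0.9 | 14.1% | 7.1% |

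The nominal rates for a single test are 5% and, in the favourable direction, 2.5%. With 15 measures the two-sided range is 45.7% to 14.4%.

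**4. Which part of the range is plausible.** The measures overlap heavily. BMC and aBMD come from the same scan at each site, hip structural analysis and 3D-DXA are derived from the hip scans, and cortical sBMD is cortical thickness multiplied by cortical vBMD. Independence is therefore only an outer reference, and the correlated rows are the fair range.

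**5. With one declared variable.** A single primary test at 0.05 has a 5% error rate by construction. For comparison, Bonferroni over 14 measures would use 0.05 / 14 = 0.00357 each, with a familywise error of 4.4% at ρ = 0.3 and 1.4% at ρ = 0.9.

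**The case against.** The best defence is that the plan does single out one variable in advance, with a clinical reason, and that the analysis section already fixes the time contrast, the baseline covariate and the z-score scale. On that view femoral neck aBMD is the implied primary endpoint and only a label is missing. In addition, this is a journal article, and multiplicity procedures and testing order are commonly left to an analysis plan or full protocol that is not shown.

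Much of this stands. The lack of a multiplicity rule is not charged here, and the remedy is short because most of its parts are already written. But a variable used for sizing does not become the primary endpoint by inference when the outcomes sections state something broader. The article does not leave the primary outcome to another document. It states it three times, each time as a domain.

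A reader might infer more than the text supports:

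- **That all 14 measures will be tested at 0.05.** The level appears only in the sample size calculation; the analysis section gives none.
- **That one significant measure would be declared a success.** No success rule is written; the plan merely fails to exclude this one.
- **That the powered variable is not the one that will decide.** The document does not say what decides.
- **That the chance of a false claim is 51%.** That needs 14 independent tests, which the shared scans and formulas rule out as a realistic case.

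**Conclusion.** The point holds as an undeclared primary variable. At least 14 bone measures sit under one primary heading, none is named as deciding, and the variable that was sized is absent from the outcomes sections. This part can be read directly from the document and needs no statistical assumption.

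The size of the consequence is conditional. If a claim could rest on any one of the 14 measures at two-sided 0.05, the chance of at least one false positive would be about 14% to 44%, and of one favouring exercise about 7% to 22%. These figures assume no true effect on any measure, a common pairwise correlation between 0.9 and 0.3, and measures oriented so that higher is better. Even the lowest values are nearly three times their nominal rates (14.1 / 5 = 2.8; 7.1 / 2.5 = 2.8). The matter should be settled before unblinding because it determines what the trial may conclude.

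**What to change.** Before unblinding, add a dated statement to the protocol or analysis plan that declares one primary endpoint consistent with the Sample size and Statistical analysis sections: femoral neck aBMD as an age- and sex-adjusted z-score, between-group difference at T1 (9 months), adjusted for baseline. Name the femoral neck among the DXA outcomes and align the Outcomes wording with the declaration. If a full protocol or analysis plan already names this variable, the change is only to bring the outcomes text into line.

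Make every other DXA, hip structural, trabecular bone score and 3D-DXA measure secondary. Either report these with confidence intervals and no confirmatory claim, or test them under Holm or a fixed hierarchy.

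The change is one of wording. It requires no further participants or measurements, since the trial is already sized on this variable. The downside is that a positive result only at another site or on another measure becomes secondary evidence.

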### Primary outcome: bone health

#### Dual-energy X-ray Absorptiometry (DXA)

A DXA (Hologic Series Discovery QDR, Bedford, MA, USA) will be used throughout the study to obtain BMC (g) and aBMD (g/cm^2^) for the hip, lumbar spine and total body less head. Furthermore, lean soft tissue mass (g), fat mass (kg) and body fat percentage (%) for the whole body will be obtained from total body scans. APEX software (version 4.0.2) will be used to analyse the scans following the recommendations for children and adolescents [70]. Equipment calibration, participant setting and scan analyses will be performed by the same researcher. DXA uses a minimal radiation (i.e. spending a day outside in the sunshine) and the effective dose for the scans in children has been set in 3–6 μSv [71].

##### Hip Structural Analysis (HSA)

HSA is a DXA-based software that analyses hip scans to estimate bone geometric properties of the proximal femur. This software analyses structural characteristics through the distribution of bone mineral mass in a line of pixels across the bone axis [72]. These geometric estimates in the proximal femur will be derived from: 1) the cross-sectional area (mm^2^); 2) section modulus (mm^3^); and 3) the cross-sectional moment of inertia (mm^4^). For these variables, the short-term coefficient of variation has been reported to be between 2.4 and 10.1% [73].

##### Trabecular Bone Score (TBS)

TBS is a DXA-based software (iNsight version 3.0, Medimaps, Pessac, France) that indirectly assesses the state of trabecular microarchitecture in the lumbar spine. Based on experimental variograms of the projected DXA image, TBS evaluates the heterogeneity of the grey-levels pixels of the aBMD and higher heterogeneity implies worse trabecular connectivity [74]. Low values reported in this parameter have been associated with a higher fracture risk, and therefore it is considered an index of bone quality [75]. The short-term coefficient of variation for TBS has been reported to be between 1.7 and 2.1% for spine aBMD in 92 individuals with repeated spine DXA scans performed within 28 days [76].

